#### Assessment

For all subjects, radiographs will be performed at the 2 week, 6 week and 3 month follow-up. The 2 week appointment will involve a clinical assessment to exclude early complications related to the fracture or surgery, and a routine radiograph to evaluate the fracture position. The 6 week appointment will involve a clinical assessment of fracture healing and a routine radiograph to assess union. Radiological union will be assessed by the principal investigator at each site. If the fracture is radiographically united at 6 weeks no radiographs will be performed at the 3 month appointment. In cases where there is doubt as to the degree of union at 3 months the radiographs will be reviewed by a principal investigator from another site. Clinical data of union including fracture mobility, tenderness and pain will also be obtained at each follow-up. The x-rays of the first 40 subjects' will be reviewed by an independent, blinded radiologist, once the principal investigator has judged the fracture to have united or be un-united. If there will be a discrepancy of opinion greater than 2% (1 patient), this process will be continued for all trial patients. For those radiographs where there is a discrepancy of opinion, the Chief Investigator will review the case and a majority consensus opinion will be gained from 3 Principal Investigators.

The Constant-Murley [19] and Disability Arm Shoulder and Hand score (DASH) [20] scoring systems will be performed at the 3 month and 9 month reviews. The Constant-Murley score [19] is a practitioner completed objective score on a scale of 100 points divided into section for pain, activity, range of movement and strength and is measured for both arms. The Constant-Murley Score is one of the most used shoulder evaluation tool. This scoring system includes both physical examination tests and subjective evaluations by the patients allowing a functional assessment of the shoulder independently by the specific type of disorder. The Constant-Murley Score is divided into 4 subscales: Pain (15 points); Activities of daily living (ADL) (20 points); Range of Motion (ROM) (40 points) and Strength (25 points). The Pain and the ADL scales are self-reported by patients: in the first version of the Constant-Murley Score, the pain scale was scored as none (15 points); mild (10 points); moderate (5 points) and severe (0 points). In the revised version of 2008, the pain scale is scored by a VAS. The ADL score is divided into 4 items: Sleep, 2 points; Work and Recreational Activities/Sport 4 points each; Positioning the Hand in the Space, 10 points. ROM is evaluated as the active elevation of the arms on the sagittal and lateral planes and the internal and external rotation of the shoulders, 10 points each. Finally, strength is evaluated as the number of pounds of pull that the patient can resist in abduction to a maximum of 25 points. The total possible score is 100 points, indicating an asymptomatic and healthy person, while the worst score is 0 points. The validity and responsiveness of Constant-Murley Score were evaluated in successive studies [22]. Evaluating construct validity, the Constant-Murley Score showed strong correlation with other scales. Evaluating reliability, ICCs varied from 0.84 to 0.87.

The DASH score [20] is a patient completed subjective score with 30 analogue scale responses producing a score between 0 and 100 points. The DASH score is a standardized questionnaire that assesses the symptoms and functional status in people with different upper extremity musculoskeletal disorders. The questionnaire consists of three sections: Symptoms, Sport and Music, Work. The first section is composed by 30 items and evaluates symptoms and functional status at the level of disability. The second and third sections are an optional module of four items for Sport and Music and four items for Work. Each item is scored with a five point scale: 1 = no difficulty; 2 = mild difficulty; 3 = moderate difficulty; 4 = severe difficulty; 5 = unable. The result of each module is summed and transformed to obtain the DASH score ranging, for each section, from 0 (no disability) to 100 (severe disability). Relatively to Internal Consistency the DASH has shown in multiple tests to have a high Cronbach's alpha (0.97); the responsiveness of the questionnaire (to self-rated or expected change) was comparable with or better than that of the joint-specific measures in the whole group and in each region [23].

An independent physiotherapy practitioner not involved in patient's surgical care or rehabilitation program will administer both assessment tools. There will a different examinator in each centre, who will be trained for the purpose of this study. The Constant score will be performed in a standardized way, using the same dynamometer in all the centres.

In the event of a patient developing a non-union at 12 weeks or more, he/she will exit the trial and be offered surgical management. Data regarding treatment offered and pursued will be collected.

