**Methods/Design:**

We aim to undertake a multicentre randomised controlled trial evaluating the effectiveness and safety of conservative management versus open reduction and internal fixation for displaced mid-shaft clavicle fractures in adults. Surgical treatment will be performed using the Acumed clavicle fixation system. Conservative management will consist of immobilisation in a sling at the side in internal rotation for 6 weeks or until clinical or radiological union. We aim to recruit 300 patients. These patients will be followed-up for at least 9 months. The primary endpoint will be the rate of non-union at 3 months following treatment. Secondary endpoints will be limb function measured using the Constant-Murley Score and the Disabilities of the Arm, Shoulder and Hand (DASH) Score at 3 and 9 months post-operatively.

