### Sample size

Based on a comparison of the percentages of patients with a non union at 12 weeks following treatment, it is estimated that 141 patients will be required in each treatment group to detect at least a reduction in percentages from 15% [6] to 5% non union with 80% power and a significance level of 5% [25]. A 4% non union rate has been quoted in the literature [26], however for the purposes of this calculation we have used a 5% as a maximum acceptable clinical failure rate. By randomising 300 patients (150 per group) the study will be adequately powered with allowance for loss to followup. Recruitment of 300 subjects will also ensure at least 80% power to detect clinically important effects for secondary outcomes. For the DASH score this will allow detection of a 3.3 point difference in mean scores with a significance level of 5% (assuming a standard deviation of 10) [20]. For the Constant-Murley score a 5 point difference in mean scores will be detectable at a 5% significance level (assuming a standard deviation of 14.5) [19]. Calculations have assumed approximate Normality of the scores [25].

It is estimated that 13 patients per month will be recruited to the study. This would lead to a total period of recruitment for the trial of 23 months.

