### Data Analysis

The success of randomisation will be made in a visual comparison of the baseline characteristics of those randomised to the two groups: centre, age, gender, side of injury, mechanism of injury, fracture classification [21] and ASA grade.

The representativeness of the groups randomised to the trial will be examined by comparing their baseline characteristics with those who were eligible but refused to participate.

The primary outcome is the rate of non union in each group at 3 months. Secondary outcomes are Constant-Murley and DASH scores at 3 months and 9 months following injury.

All of the analyses will use the intention-to-treat principle. The primary outcome will be compared between the conservative and operative groups using generalised linear regression models both unadjusted and adjusted for centre (the stratification factor), age, fracture classification and ASA grade. Estimates of the difference in proportions and odds ratio with associated 95% confidence intervals will be obtained.

The Constant-Murley and DASH outcomes will be compared between groups using analysis of covariance. This will allow for a baseline score as suggested through measurements recorded for the other normal limb. The assumptions of this approach will be checked using summary information and graphs. If assumptions are not met, appropriate data transform or non parametric methods will be considered. Multiple regression models will be used to investigate the intervention effect after adjustment for centre, age, fracture classification and ASA grade.

Where outcome data are missing, a check of the characteristics of those with and without the outcome of interest will be carried out to ensure that missing data have not biased a comparison based on complete data. All analyses will be carried out using Stata.

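### Patients with non-union leave the trial from 12 weeks, which conflicts with 9-month follow-up of all patients and intention-to-treat, and leaves the 9-month scores to a subset selected by the primary outcome

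*Protocol article*

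**What the plan says.** The last paragraph on follow-up in the Assessment section gives the rule: "In the event of a patient developing a non-union at 12 weeks or more, he/she will exit the trial and be offered surgical management". The next sentence names what is recorded afterwards: "Data regarding treatment offered and pursued will be collected". It does not mention functional scores for these patients.

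Other parts of the protocol assume that everyone is followed and scored:

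- The abstract (Methods/Design) says of the 300 patients: "These patients will be followed-up for at least 9 months". The Time-points section schedules the last visit for all patients between 9 and 12 months from randomisation.
- Assessment says that the Constant-Murley and DASH "scoring systems will be performed at the 3 month and 9 month reviews". Endpoints and Data Analysis make the 9-month scores secondary outcomes.
- Data Analysis says: "All of the analyses will use the intention-to-treat principle". On the functional scores it adds: "The Constant-Murley and DASH outcomes will be compared between groups using analysis of covariance".
- For missing outcomes, Data Analysis plans a comparison of the characteristics of patients with and without the outcome, "to ensure that missing data have not biased a comparison based on complete data".
- Sample size powers the trial "to detect at least a reduction in percentages from 15% [6] to 5% non union".

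**The concern.** The event that takes a patient out of the trial is the primary outcome itself, and the design expects it to be three times as common in one arm as in the other. If the rule is followed literally, the 9-month comparison covers only patients whose fracture had united. That group is formed after randomisation, partly by the effect of treatment, so randomisation no longer protects the comparison.

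Treatment failures are likely to be among the poorer scorers, and more of them would be missing from the conservative arm. The better surgery prevents non-union, the more conservative-arm failures would disappear from the functional comparison. The protocol gives some support for expecting poorer scores: its rationale cites evidence of inferior results after treatment of non-union.

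The planned missing-data check does not help. It compares patient characteristics, whereas here the scores are missing because treatment failed. Similar characteristics would give false reassurance. A separate analysis plan could not recover scores that were never collected.

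**Working it through.** **Inputs from the protocol.** Non-union 15% against 5%, read as conservative against operative; 80% power; 5% significance, taken as two-sided because the sidedness is not stated; 141 required and 150 randomised per group; DASH difference 3.3 with SD 10; Constant-Murley difference 5 with SD 14.5 (all Sample size). A further 10% lost by final follow-up (Recruitment).

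**1. The plan's own figures.** Two proportions, pooled variance, no continuity correction:

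n = [1.96 × √(2 × 0.10 × 0.90) + 0.842 × √(0.15 × 0.85 + 0.05 × 0.95)]² / 0.10² = (0.832 + 0.352)² / 0.01 ≈ 140.1, rounded up to 141 per group. This matches.

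For the scores, power = Φ(δ / [SD × √(1/n₁ + 1/n₂)] − 1.96). With 150 per group:

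- DASH: 3.3 / (10 × √(2/150)) = 2.858, giving 81.5%.
- Constant-Murley: 5 / (14.5 × √(2/150)) = 2.986, giving 84.8%.

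The stated power of at least 80% therefore reproduces, provided that all 300 patients are scored.

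**2. Expected exits at the design rates.**

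- Conservative: 150 × 0.15 = 22.5, leaving 127.5.
- Operative: 150 × 0.05 = 7.5, leaving 142.5.

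That is 30 patients in all, split 3 to 1.

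**3. Power at 9 months.** The same formula with the reduced numbers gives:

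| Situation | Conservative / operative | DASH | Constant-Murley |
|---|---|---|---|
| All randomised patients scored | 150 / 150 | 81.5% | 84.8% |
| Exits only | 127.5 / 142.5 | 77.2% | 80.7% |
| Exits and further 10% loss | 114.75 / 128.25 | 72.8% | 76.5% |
| 10% loss only, exited patients still scored | 135 / 135 | 77.4% | 80.9% |

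Under the protocol's own 10% loss, the exit rule therefore costs 77.4 − 72.8 = 4.6 percentage points of DASH power and 80.9 − 76.5 = 4.4 points of Constant-Murley power.

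**4. Shift in the between-arm difference.** Suppose that at 9 months patients with non-union score Dc points worse than united patients in the conservative arm, and Do points worse in the operative arm. Each arm's mean over all its patients is worse than its united-only mean by (non-union rate × deficit). Dropping the failures therefore removes 0.15 × Dc − 0.05 × Do from the difference between arms. With an equal deficit D in both arms this is (0.15 − 0.05) × D = 0.10 × D.

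The protocol gives no value for D. With assumed values:

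| Assumed D (DASH points) | Removed from the difference | Share of the 3.3-point target |
|---|---|---|
| 10 | 1.0 | 30% |
| 20 | 2.0 | 61% |
| 30 | 3.0 | 91% |

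A smaller deficit removes less; D = 5 removes 0.5 points. D would have to be 3.3 / 0.10 = 33 for the full target to be removed. If the deficits differ between arms the result changes: Dc = 10 and Do = 30 give 1.5 − 1.5 = 0.

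**The case against.** The strongest reply is that leaving the trial may have meant leaving the allocated management only. Some data are still collected afterwards, and the Time-points section covers all patients without exception. That reading is possible, so it cannot be taken as certain that these patients would go unscored. But the exit sentence does not say this, and it names only treatment data. A site that follows it literally would not score these patients. The ambiguity is itself the defect to correct.

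A reader might infer that the trial's main result is compromised. The documents do not support that. Non-union at 3 months is ascertained at or before exit, so the primary analysis and its sample size stand. The 3-month scores are largely unaffected, because non-union is judged at about the same visit.

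A reader might also infer that information on late union is lost. This is largely unsupported: Assessment schedules no radiograph after 3 months for anyone, so at most clinical signs of union at the last visit are missed. Nor would all later surgery go unrecorded, because treatment pursued is collected.

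Three further reservations stand:

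- The size and direction of the bias depend on deficits that the documents do not give. These patients are offered surgery, and their 9-month scores are unknown.
- The 22.5 and 7.5 assume that every non-union in the sample-size calculation triggers exit. Endpoints defines non-union by radiograph alone. Adverse Events or Complications also requires pain and motion at the fracture site. The exit rule does not say which definition applies, and under the second there could be fewer exits.
- The planned missing-data check does exist, although it cannot repair this mechanism.

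**Conclusion.** The point holds for the 9-month secondary outcomes. As written, the exit rule contradicts both the follow-up of all patients to 9 to 12 months and the intention-to-treat statement. It would limit the 9-month comparison to a subset selected after randomisation by the primary outcome.

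The imbalance in exits follows from the plan's own rates, if every non-union leads to exit. The loss of power needs no assumption about how these patients score; it takes DASH below the stated 80%.

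The bias is illustrative only: 1 to 3 DASH points for an assumed common deficit of 10 to 30. It probably acts towards no difference, but that rests on patients with non-union scoring worse and on the deficit being similar in both arms. It would be wrong to conclude that a given share of the true effect is erased, because the comparison is with the target difference and not with a known effect.

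**What to change.** Reconcile the exit sentence in Assessment with Time-points and Data Analysis:

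- State that a patient with non-union has reached the primary endpoint but stays in follow-up.
- Collect Constant-Murley, DASH, complications and re-operations at the 9-month visit whatever further treatment is given.
- Analyse everyone in the arm to which they were randomised. An analysis of united patients only should be supportive at most.

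The offer of surgery stays as it is.

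The cost is a short amendment and 9-month visits for about 30 expected patients. Those visits are already in the schedule for all patients; the protocol gives no budget against which to price them. Recruitment began in December 2007 and this is the September 2010 version, so the scores of patients who have already left may not be recoverable. Their number should be reported by arm.

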#### Adverse Events or Complications

An adverse event or complication will be defined as any event that necessitated another operative procedure or additional medical treatment. Non-union will be defined as the lack of radiographic healing with clinical evidence of pain and motion at the fracture site at 3 months. Symptomatic mal-union will be defined as union of the fracture in a shortened, angulated, or displaced position with weakness, easy fatigability, pain on overhead activity, neurologic symptoms, and shoulder asymmetry with a completed or planned corrective osteotomy.

Complex regional pain syndrome will be diagnosed by the presence of dysaesthetic pain and hyperaesthesia extending into the hand of the involved limb, vasomotor changes, skin atrophy, and diffuse osteopenia [24].

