## Background

### Rationale for the trial

Clavicle fractures account for around 4% of all fractures [1] and up to 44% of fractures of the shoulder girdle [2,3]. Fractures of the middle third (or mid-shaft) account for approximately 80% of all clavicle fractures [2,3].

Management of mid-shaft clavicular fractures is often challenging and the outcome can be unsatisfactory. In particular it is not clear whether surgery produces better outcomes than non-surgical management. Traditionally mid-shaft clavicular fractures have been managed conservatively, even when substantially displaced [4].

Recent literature has highlighted the high non-union rate in displaced mid-shaft clavicular fractures, with a non-union rate up to 15% [5-7]. Furthermore, there is some evidence that conservative management affects the outcome in terms of upper limb function [8-10] and that treatment of non-unions produces inferior results [11,12]. Few comparative studies of surgical versus non-surgical treatment for mid-shaft clavicle fractures are available, and contradictory results have been obtained [13-15].

In a randomised controlled trial, though patients with mid-shaft clavicle fractures had higher functional scores at short-term follow-up after internal fixation, functional scores were similar at 6 months and 1 year. In addition, internal fixation with a modified Hagie pin was associated with a higher complication rate [13].

In a multicentre, prospective clinical trial [16], 132 patients with a displaced mid-shaft fracture of the clavicle were randomized to either operative treatment with plate fixation (67 patients) or nonoperative treatment with a sling (65 patients). Operative fixation of a displaced fracture of the clavicular shaft resulted in improved functional outcome and a lower rate of mal-union and non-union compared with nonoperative treatment at one year of follow-up. Hardware removal remained the most common reason for repeat intervention in the operative group.

A formal cost-effectiveness analysis based on the same prospective, randomized, controlled trial [14] proposed that the cost-effectiveness of open reduction and internal fixation (ORIF) after acute clavicle fracture depended on the durability of functional advantage for ORIF compared with nonoperative treatment. When functional benefits persisted for more than 9 years, ORIF had a favourable value compared with many accepted health interventions.

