Two 2009 Cochrane reviews [1,11] on the management of middle third clavicle fractures concluded that there is insufficient evidence from randomised controlled trials to determine which methods of conservative [11] and surgical [1] treatment are the most appropriate for middle third clavicle fractures.

A 2010 systematic review [17] concluded that there is moderate evidence that operative treatment for mid-shaft clavicle fractures results in a lower rate of fracture non-union and improved patient-oriented outcome compared to non-operative treatment. However, because union rates are generally high and there are complications which are unique to surgical intervention, risks have to be considered before a decision on treatment is made. The most important risk factors for non-union are major displacement and fracture comminution. Of all surgical procedures the best evidence of efficacy is presently available for plate fixation and elastic stable intramedullary nailing [17].

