### Trial aim

The aim of this multicentre randomised controlled trial (RCT) is to compare the safety and effectiveness of conservative and operative management of mid-shaft fractures of the clavicle in adults. The primary outcome will be the non-union at 3 months from injury. Secondary outcomes will be clinical scoring systems assessing pain, mobility, strength and function at 3 and 9 months follow-up.

Our null hypothesis is no difference in the non-union rate at 3 months from injury and in scoring systems at 3 and 9 months follow-up between the 2 groups.

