#### Operative Details

All procedures will be performed in an orthopaedic theatre under antibiotic cover according to local microbiology protocols in each centre. General anaesthetic will be used for all patients with or without supplementary interscalene blockade. All surgical procedures will be performed by one of the orthopaedic consultants named in the protocol or by their specialist registrar/research fellow under consultant supervision. All the patients enrolled in the study will be treated in a standardised way.

An infraclavicular incision will be used and a myo-periosteal flap elevated from the fracture segments. Fixation will be performed using the Acumed clavicle fixation system (Hillsboro, Oregon), consisting of a pre-contoured titanium plate with 2.7 mm or 3.5 mm screws. Image intensification will be available for all cases and hard copies will be obtained at the end of each procedure. Following wound closure the affected arm will be placed in an arm sling. Mobilisation and rehabilitation will be identical to the non-operative group (see below).

Data from the procedure will be documented on the operation note, including any peri-operative complications or deviations from the standard technique.

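### The adverse event definition leaves untreated harms out of the safety comparison and does not say how its general rule and its named conditions combine; it can under-count either arm

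*Protocol article*

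**What the plan says.** The section Trial aim states that the purpose "is to compare the safety and effectiveness of conservative and operative management". The section Adverse Events or Complications gives the general rule: "An adverse event or complication will be defined as any event that necessitated another operative procedure or additional medical treatment". It then defines three conditions:

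- Non-union: "Non-union will be defined as the lack of radiographic healing with clinical evidence of pain and motion at the fracture site at 3 months". No treatment is required.
- Symptomatic mal-union: malposition with a list of symptoms, ending in "shoulder asymmetry with a completed or planned corrective osteotomy".
- Complex regional pain syndrome: diagnosed on clinical and radiographic signs. No treatment is required.

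The section does not say whether these three count in their own right or only once the general rule is met. Elsewhere, Operative Details has the operation note record the procedure, "including any peri-operative complications or deviations from the standard technique". The Assessment section includes a 2-week check for early complications in both arms. It says of a patient with non-union at 12 weeks or later that "he/she will exit the trial and be offered surgical management". The Blinding section says that neither patients nor clinicians can be blinded. The Rationale acknowledges that "there are complications which are unique to surgical intervention, risks have to be considered before a decision on treatment is made" and reports from an earlier plating trial that "Hardware removal remained the most common reason for repeat intervention in the operative group".

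**The concern.** A definition that turns on treatment measures two things at once: whether harm occurred, and whether someone chose to treat it. In an open trial that choice lies with clinicians who know the allocation, and it varies with local practice and patient preference. A patient left with numbness near the incision, or with a prominent plate that is put up with, has been harmed by any ordinary understanding but is not an adverse event under this rule. The same holds for a patient whose clavicle has healed short and painful and who has no osteotomy.

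Because the general rule and the named conditions are not linked, two sites could also apply the section differently and both be following the text. At stake is the safety half of the aim. The primary endpoint does not depend on this definition.

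**Working it through.** The plan gives no figure for harms. Its only event rates are the non-union rates of 15% and 5% behind the 141 per group in the Sample size section. That number reproduces (two-sided 5%, 80% power, pooled variance, no continuity correction) but has no bearing here. The check is therefore mainly a reading of the text.

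**Step 1: which harms are counted under each reading.** Reading A: the named conditions count in their own right. Reading B: they only define terms, and the general rule still applies.

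| Harm | Arm mainly affected | Reading A | Reading B |
|---|---|---|---|
| Non-union with pain and motion, untreated | conservative, on the plan's rates | counted | not counted |
| Complex regional pain syndrome, untreated | either | counted | not counted |
| Symptomatic mal-union, no osteotomy done or planned, no other treatment | conservative | not counted | not counted |
| Lasting sensory loss or tolerated symptomatic implant, untreated | operative | not counted | not counted |

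The two readings disagree on the first two rows, so the section is ambiguous. They agree on the last two: untreated harms are lost in both arms. A mal-union that received medical treatment but no osteotomy could enter under the general rule, but not as symptomatic mal-union.

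**Step 2: can the size or direction be fixed?** Only on assumed rates. Patients missed = 150 × (share harmed) × (1 − share meeting the treatment condition), with 150 per group from the Sample size section.

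- Operative arm, assuming 10% to 30% have a surgery-specific harm and 30% to 70% of those are treated. Lowest: 150 × 0.10 × 0.30 = 4.5. Highest: 150 × 0.30 × 0.70 = 31.5. That is about 5 to 32 patients, or 3 to 21 percentage points.
- Conservative arm, assuming 5% to 20% have symptomatic mal-union, 10% to 50% of those have an osteotomy done or planned, and the rest have no other treatment. Lowest: 150 × 0.05 × 0.50 = 3.75. Highest: 150 × 0.20 × 0.90 = 27. That is about 4 to 27 patients, or 2.5 to 18 percentage points.

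Net difference (operative missed minus conservative missed) at the extremes: 31.5 − 3.75 = 27.75 more missed in the operative arm, or 4.5 − 27 = −22.5, that is 22.5 more missed in the conservative arm. With 20% harmed and half meeting the treatment condition in each arm, both miss 15 and the net is zero. The sign is not determined.

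**The case against.** The strongest defence is that the test is the same for both arms and that a need for treatment is a recognisable threshold of importance. Additional medical treatment is a broad category. Peri-operative complications go on the operation note without a treatment condition, the 2-week visit looks for early complications in both arms, and a troublesome plate can show in the Constant-Murley and DASH scores. A detailed list of surgical events belongs on a case report form, and an article need not print it.

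Much of this stands. The absence of such a list is not a fault, nor is the absence of an adverse event analysis from the Data Analysis section, which an analysis plan may supply. But the counting rule is stated here in full, and it excludes untreated events. An entry on the operation note does not become an adverse event under that rule. The 2-week check concerns early complications only. Functional scores do not identify which harm occurred.

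A reader might go further and infer that the rule favours surgery, because non-union and complex regional pain syndrome are defined by findings while surgery-specific harms have only the treatment-based test. The documents do not support that:

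- The mal-union definition is the strictest of the three. The osteotomy is an added condition, so the cases it drops fall mainly in the conservative arm.
- Complex regional pain syndrome is not tied to either arm.
- Non-union leads to an offer of surgery, so it would largely meet the general rule anyway.
- An event that puts a patient on a list for plate removal can fairly be said to have necessitated a procedure.
- Counting on findings alone is only Reading A.

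Nor can one say that every non-union in the primary endpoint also counts as an adverse event. The Endpoints section requires only lack of radiographic healing, whereas the adverse event section adds pain and motion.

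**Conclusion.** The point holds as a fault in a stated rule. Untreated harms fall outside the adverse event definition in both arms, counting depends on unblinded treatment decisions, and the section does not say how its general rule and its named conditions combine. This weakens the safety comparison but leaves the primary endpoint untouched. It should be corrected.

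The size is unknown. The ranges in the working rest wholly on assumed harm and treatment rates and show only that the loss could be material in either arm and could run in either direction. They do not estimate a bias, and a loss of power for a safety test cannot be derived from them.

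**What to change.** Rewrite the section Adverse Events or Complications around one counting rule for both arms:

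1. At each existing visit, record any untoward event that affects the injured limb or arises from the allocated treatment, whether or not it is treated.
2. Report, as a severity level in both arms, whether the event needed a further operation (completed or planned) or additional medical treatment.
3. Count symptomatic mal-union both with and without osteotomy, and show the two separately.
4. State that non-union, mal-union and complex regional pain syndrome count under this same rule.

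The cost is a change of wording and some additional recording at visits that already take place. More minor events will be listed. The severity level keeps a count on the present treatment-based definition available.
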